### MSM Setup

Data required for fitting MSMs include care occurrences and corresponding event times to characterize state occupancy and transitions over time, along with time-invariant and time-varying covariates. SUD-related medical conditions will be incorporated as covariates when they are expected to influence care type or care setting. Additional details are provided in the analysis section. The time scale for the MSMs is continuous calendar time, with time since entry into each state reset to 0 (“clock reset”) at state entry for modeling transition intensities.

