**Figure 1. F1:**
[figure not shown]
Graphical representation of the multistate model. Notation: Subcohort: [*C*_*1*_; care states (*S*_*1*_,...,*S*_*15*_); discontinuation of care: *D*; SUD remission state: *R*; terminal states: (*T*_1_,...,*T_4_*); *t*: time, *p*: probability] The 3 dots connecting the states indicate that the depicted relationships are possible for the other states not shown in this figure. p: probability; SUD: substance use disorder; t: time.

We will adopt a semi-Markov assumption [59] under which transition intensities depend on only the duration that patients spend time in the current state before transitioning. This framework allows transition intensities to vary over time rather than assuming constant transition intensities as in the Markov framework. Time is defined as the duration since entry into a state, with the clock reset to 0 upon entry into the cohort and each subsequent state. At any time since entry into the initial state, a patient occupies 1 of the 21 states (17 transient states and 4 terminal states). Movements between states *j* and *k*
$\left(j,k=S_{1},\ldots ,S_{15},D,R,T_{1},\ldots ,T_{4}\right)$, are governed by a 21-by-21 matrix of transition intensities $q_{jk}(t,z(t))$, which is a function of time *t* and covariates z(t). Intensities capture the instantaneous probability of moving from state *j* to *k*.

Under the semi-Markov assumption, we will fit separate flexible parametric survival models [60,61] for each transition:

$\log\{q_{jk}(t,z(t))\}=s(\log(t)|\eta ,k_{0})+\beta^{T}z_{i}(t)$.

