For simplicity, we omit transition-specific subscripts for the parameters $\left(\eta ,k_{0},\beta \right)$. In the model, $s(\log(t)|\eta ,k_{0})=\sum_{i=1}^{k_{0}}\eta_{i}B_{i}(\log(t))$ represents the log cumulative baseline intensity function, which we model flexibly using restricted cubic spline basis functions (also known as natural cubic splines) $B_{i}(\cdot )$, with corresponding coefficients $\eta_{i}$. The number of knots, $k_{0}$, determines the number of basis functions and thus the flexibility of the baseline intensity functions. For covariates *z*_*i*_(*t*), the coefficients β represent the log hazard ratios at time t. The unknown parameters to be estimated or selected from data are $\left(\eta ,k_{0},\beta \right)$. We will use the Akaike information criterion based on data to select the number of knots, with lower Akaike information criterion values indicating better model fit. The regression coefficient parameters (η,β) will be estimated by using the maximum likelihood approach for statistical inference [62,63]. For each transition, we will include prespecified covariates for adjustment when the number of transitions allows (at least 10 transition events per covariate), and if additional covariate selection is required, variables that are statistically significant at the 5% level based on Wald tests will be included [64]. The estimated transition intensities are transformed to a transition probability from states j to k at time t since entry into state j at time s (s<t, s and *t*>0), by integrating, $p_{jk}(s,t)=\exp\left\{-\int_{s}^{t}q_{jk}(u,z(u))\;du\right\}$.

Multiple incident SUD events may be observed within the same patient (see Quantitative Study Population). For example, a patient may have an incident SUD event, eventually experience a terminal state such as ceasing SUD care (eg, one who receives no SUD care for 194 days), and then experience a second incident SUD event. Including multiple incident events from the same patient within the same subcohort in the MSM framework may introduce within-patient correlation and reflect care pathways that differ from those of the initial episode. We will account for within-patient correlation using a sandwich variance estimator for the parameter estimates. The number of prior incident events will be included as a covariate or used as a stratification factor, depending on its distribution.

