To assess model adequacy, we will compare spline-based estimates of the cumulative baseline hazard with nonparametric estimates derived from the Kaplan-Meier method for visual agreement. To evaluate the proportional hazards (time-independent effects) assumption, we will test for time-dependent effects by including interactions between covariates and spline functions of time. If these interaction terms are not statistically significant at the 5% level, they will be excluded from the final model.

Additionally, we assume that transition times are exactly observed. Lastly, it is assumed that the distribution of health care visit times is independent of transition probabilities for simplicity (noninformative visiting process). We will primarily use the R (R Foundation) package *flexsurv* to implement the MSMs and develop our own modules to transform the fitted results to answer research questions.

We will consider sensitivity analyses if sample size and other feasibility constraints permit. This includes stratified analyses by subgroups defined by the number of outpatient visits (eg, patients with more visits may have poorer health) [65,66] or clinically meaningful periods. For instance, impactful operational changes occurred due to COVID-19 mitigation restrictions (eg, reduced in-person care), so we will consider estimating models before, during, and after these restrictions were in place. Additionally, stratified analyses by SUD type will be considered to acknowledge that each substance may sometimes require unique forms of care, such as pharmacotherapy usage.

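### The printed transition probability integrates a time-since-state-entry intensity from the entry time s to t, which conflicts with the clock-reset semi-Markov model for any state entered after time 0

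*Protocol article*

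**What the plan says.** Two places in the protocol article define the time argument of the intensity q_jk, and they agree.

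- **MSM Setup.** The sentence opens with "The time scale for the MSMs is continuous calendar time" and continues "with time since entry into each state reset to 0 (“clock reset”) at state entry for modeling transition intensities".
- **Statistical Analyses, Aim 1 (semi-Markov paragraph).** "Time is defined as the duration since entry into a state, with the clock reset to 0 upon entry" to the cohort and to each later state. The adopted assumption is that "transition intensities depend on only the duration that patients spend time in the current state before transitioning". The stated reason for it is: "This framework allows transition intensities to vary over time rather than assuming constant transition intensities as in the Markov framework".

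Later in the Aim 1 text the fitted intensities are turned into "a transition probability from states j to k at time t since entry into state j at time s", with s below t and both positive. The printed expression is p_jk(s,t) = exp{−∫ from s to t of q_jk(u, z(u)) du}.

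The models will be fitted mainly with a standard R package, but the team will also "develop our own modules to transform the fitted results to answer research questions". Study Outcomes says that the guideline-concordant care outcomes are derived from the estimated transition probabilities.

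**The concern.** Under a clock-reset model, a patient who enters state j at episode time s has been there for duration u−s at episode time u. The intensity that applies is therefore q_jk(u−s). The printed integral uses q_jk(u) instead. It skips the first s days of the intensity curve and reads off a later stretch that the patient has not reached.

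Entry times differ between patients for every state after the first. Coded literally, the formula would make the chance of leaving a state depend on how late in the episode it was entered, which the adopted assumption rules out. The outputs exposed are those that chain several stays, such as occupancy over time since cohort entry and sequence probabilities under Aim 2. The formula matters in practice because it is the only one the article prints for this step, and study-written code will carry the step out.

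**Working it through.** The documents state no figure on this point, so there is nothing to reproduce. The check has two parts.

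**1. Which clock can s and t be on?**

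- *Both on the reset clock (durations in j).* The integral from s to t would then be a valid conditional quantity for a patient still in j at duration s. But the text calls s the time of entry into j and requires s>0, whereas entry on the reset clock is 0. This reading does not fit.
- *Both on the episode clock.* Entry at s>0 makes sense, but q_jk must then be evaluated at u−s. The printed integrand is q_jk(u).
- *t a duration since entry, s an episode time.* The two limits then lie on different clocks, and the condition s<t has no clear meaning.

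No reading makes the wording, the limits and the clock-reset definition consistent. Nothing else in the article redefines s or t.

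**2. What the limits do (illustration only).** Assumed: one exit and a Weibull cumulative intensity H on time since state entry.

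*Example A, probability of leaving within 30 days.* Take H(d) = ln2 × (d/30)^a, so that 1 − exp{−H(30)} = 0.50 whatever the entry time under clock reset. The printed limits give 1 − exp{−[H(s+30) − H(s)]}. For a = 0.5 and s = 30, H(60) − H(30) = 0.693 × (1.414 − 1) = 0.287, and 1 − exp(−0.287) = 0.25.

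| Shape a | Clock reset, any s | Printed limits, s=30 | s=60 | s=180 |
|---|---|---|---|---|
| 0.5 (falling) | 50% | 25% | 20% | 13% |
| 0.75 (falling) | 50% | 38% | 34% | 28% |
| 1 (constant) | 50% | 50% | 50% | 50% |
| 1.5 (rising) | 50% | 72% | 81% | 93% |

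This example uses the complement, 1 − exp(−integral), because the printed exponential is a probability of not leaving.

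*Example B, the exponential exactly as printed.* Take H(u) = (u/30)^a and a 14-day window. For a = 0.6 and s = 30, H(44) − H(30) = 1.258 − 1 = 0.258, and exp(−0.258) = 0.772. With limits 0 to 14, H(14) = 0.633 and exp(−0.633) = 0.531.

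| Shape a | Clock reset, any s | Printed, s=0 | s=30 | s=180 |
|---|---|---|---|---|
| 0.6 | 0.531 | 0.531 | 0.772 | 0.874 |
| 1.0 | 0.627 | 0.627 | 0.627 | 0.627 |
| 1.5 | 0.727 | 0.727 | 0.460 | 0.174 |

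The two forms agree when s = 0 or when the intensity is constant. The first is outside the stated range of s, and the model was chosen so as not to assume the second.

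**A related defect in the same line.** Correcting the limits does not by itself yield a transition probability. The printed exponential equals 1 at t = s and ignores competing exits. With assumed constant rates of 0.03 (j to k) and 0.02 (another exit) per day over 14 days, it gives exp(−0.42) = 0.657. The cumulative incidence of j to k is (0.03/0.05) × (1 − exp(−0.70)) = 0.302. Conversely, repairing the competing exits while keeping the limits s to t would leave the clock error in place.

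**The case against.** The best defence is that the clause is badly worded and nothing more: it speaks of t as time since entry, which is a duration, and with s on the same scale the integral is a familiar conditional quantity. That would hold if s were time already spent in j. The text instead makes s the moment of entry, and positive, so the defence fails on the wording, though the authors may have intended it.

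Other parts of the defence stand:

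- **Calendar time.** A reader might infer from MSM Setup that q_jk has a third, calendar-time argument. Read in full, that sentence puts the intensities on the reset clock, in agreement with Aim 1. Calendar time there is naturally the scale on which events are observed.
- **Reach.** A reader might infer that all Aim 2 results are affected. They are not. The 7-day and 30-day follow-up measures after an emergency department visit start in the initial state, as does the 14-day example in Table 4, so s = 0. The restricted mean survival times are defined from entry into the care state and are already on the reset clock. Sequence probabilities are detailed in Multimedia Appendix 2, which is not shown, so distortion there cannot be asserted.
- **Coding.** Harm arises only if the line is coded literally. A correct clock-reset routine would avoid it, and nothing shows that the study's modules will ignore the reset.
- **Precedence.** The exponential has to be replaced anyway, and a correct semi-Markov formula written on duration would settle the limits too.

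**Conclusion.** The inconsistency is real and confined to one formula. MSM Setup and the semi-Markov paragraph define q_jk on time since entry into the current state. The probability formula then evaluates it from an entry time s>0 to t, which is a clock-forward calculation. If implemented as printed, probabilities for states entered after time 0 would vary with entry time, contrary to the model. They would be too low for exit where intensities fall with time in state and too high where they rise. There is no error at s = 0 or under constant intensities.

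The size cannot be stated. The percentages above rest on an assumed Weibull shape and a single exit, in a model with 21 states, and Example A also uses the complement of the printed expression. They show direction only and should not be read as estimates of bias in this study. The point is worth correcting because study-written modules will do this transformation and the article offers no other formula for it.

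**What to change.** In the Aim 1 text:

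1. State one clock for q_jk, namely duration since entry into the current state, and say which clock s and t are on.
2. With s and t on the episode clock, evaluate q_jk at u−s, or equivalently integrate over durations 0 to t−s. Make this change as part of replacing the printed exponential with a transition probability that accounts for competing exits and later transitions.
3. Say that quantities over time since cohort entry are built from successive stays with the clock reset at each entry, for example by simulation from the fitted models.

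In MSM Setup, at most add a clarification that calendar time is the observation scale and not the argument of q_jk.

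The cost is an edit to text and a formula, with no new data. The Results section puts completion of final quantitative data collection at November 2027, which leaves time to correct the specification before the final analysis.

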### Quantitative Study Population

This study’s cohort will include patients who receive care for SUD. Eligible patients are adults aged 18 years and older with an incident SUD identified between January 1, 2017, and May 31, 2025. We will include both group practice enrollees, who receive most of their care from internal KPWA-owned and operated clinics, and KPWA health insurance plan enrollees who primarily receive care outside the internal delivery system (IDS). Incident SUD is defined as meeting any of the following criteria at a clinical encounter with no prior SUD indicators in the past 6 months: (1) a newly documented SUD diagnosis, or (2) two or more *DSM-5* (*Diagnostic and Statistical Manual of Mental Disorders, Fifth Edition*) symptoms reported on standardized patient symptom checklists. The index date will be the date of the qualifying incident SUD event. The 6-month “washout period” is used to define new treatment, modeled on National Committee on Quality Assurance definitions [36], but we may explore the sensitivity of sample definitions using other time frames, such as 60 days [37]. For patients who have been enrolled in KPWA for less than the length of the washout period, we will consider their first SUD event to be an incident SUD event. Provisionally, multiple qualifying incident SUD events from the same patient will be included in the analysis (see details in Statistical Analyses). Patients will be excluded from the analyses if they have opted out of research participation with the health plan (≈0.2%).

The analytic sample will be split into distinct study subcohorts comprising patients with incident SUD identified in the specific clinical settings. We anticipate using five subcohorts, including: (1) primary care, (2) urgent care, (3) ED or hospital, (4) behavioral health, and (5) all other settings. These locations are identified based on EHR and insurance claims data that code clinic departments, places of service, encounter types, and SUD diagnosis data available in each location (Table 1). Once patients are identified as having an incident SUD and meeting the inclusion criteria described above, they enter the initial state of the MSM.

**Table 1. T1:** Study subcohorts defined by the clinical setting in which an incident substance use disorder event occurs. Incident SUD^a^ events are identified for adult patients aged 18 years and older and are categorized into 1 of the 5 subcohorts in this table.

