### States for the MSMs

States will capture 3 types of events related to SUD care: initial states, transient states, and terminal states. Defining states requires a balance of specificity to produce actionable information, and parsimony to allow for an estimable statistical model with accurate estimates and smaller SEs.

Initial states in the MSMs represent the clinical settings that triggered an incident event at the start of an SUD care episode, corresponding to the 5 subcohorts in Table 1.

There are 3 types of transient states. The first type is care states, which include different types of care provided in the health care system to treat the SUD, defined by combinations of setting and service type (Table 2). We opted to define 15 preliminary SUD care states based on a combination of 3 settings and 5 service types. The second type of transient state is temporary discontinuation of care. Entry into the temporary discontinuation care state is triggered using a clinically meaningful threshold for time elapsed between SUD treatment visits. The last transient state is SUD remission, which represents an improvement in the patients’ disease.

**Table 2. T2:** Transient states and terminal states are represented in the multistate models.

Category	States included	Description
Transient states	A total of 17 transient states include 15 care states derived from crossing 5 service types with 3 care settings; temporary discontinuation of SUD^a^ care; and remission of use disorder.	Care states Service types Evaluation and assessment Behavioral treatment and counseling Prevention, education, and case management Pharmacotherapy Other service Settings Outpatient Intensive outpatient Inpatient or residential Other transient states Discontinuation of SUD care A lack of SUD care over a specified period^b^ Remission of use disorder Low risk score on alcohol and substance use screen; clinically meaningful reduction on screening scores or <2 symptoms on *DSM-5*^c^ checklist; SUD remission diagnosis
Terminal states	4 states representing the end of a care episode	Death, derived from dates in health care enrollment records or Washington State death data Loss to follow-up, defined as at least 31 days without KPWA insurance coverages Ceased SUD care (no medication fills or services with a qualifying SUD diagnosis for more than 194 days Administrative censoring (in the middle of a care episode when data collection ends)

a SUD: substance use disorder.

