### Data Used to Construct States

#### Health Care Encounter Data

We will use health care encounter data drawn from KPWA EHR data and health care insurance claims to construct initial states, transient states, and terminal states. Data elements include *ICD-10* (*International Classification of Diseases, Tenth Revision, Clinical Modification*) diagnosis codes, health care service procedure codes, encounter type classifications (eg, inpatient, ambulatory, virtual visit, or ED), encounter subtypes (eg, urgent care), departments (eg, mental health), clinical specialty (eg, mental health, social worker, or psychiatry), revenue codes, and place of service codes. Visit timestamps are used in models to determine follow-up time and transition times.

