#### Substance Use Data

Patient self-reported substance use frequency, patient self-reported SUD symptoms, and clinician-documented SUD diagnoses will be used to construct states. In the creation of initial states, diagnosis codes, service procedure codes, and revenue codes help determine whether a given health care visit was related to SUD. For instance, some initial states are defined by a new clinician-documented SUD diagnosis, while others are also defined to capture clinical workflows where patients are first identified as having substance use by the nature of a health screening (eg, substance use screening in primary care). Care states require an accompanying clinician-documented SUD diagnosis, unless the care state involves a procedure or medication that is solely indicated for SUD (eg, outpatient addiction treatment or disulfiram medication). The SUD remission state is captured using self-reported substance use frequency and SUD symptoms, and clinician-reported SUD remission diagnoses.

To obtain patient self-reported substance use frequency data, clinicians are prompted by the EHR to conduct annual screening with patients in primary care. During in-person visits, screenings are administered on paper or tablet by medical assistants, then entered into the EHR. In telephone or video visits, patients complete a questionnaire via an online patient portal. Validated substance use screening measures assess past-year alcohol, cannabis, and other drug use [32,39,40]. Patients with screening scores that are deemed to be at high risk for SUD are asked to complete a follow-up assessment for symptoms of SUD using the Alcohol Symptom Checklist and the Substance Use Symptom Checklist, respectively. These 11-item checklists capture symptoms of SUD that align with the 11 *DSM-5* diagnostic criteria [41]; the cutpoint of 2 or more symptoms is consistent with SUD. The checklists have demonstrated strong psychometric properties [42-44].

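### Transition times are assumed exact and visits noninformative with no exception for remission, which is found only at assessments and whose screening routes are annual

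*Protocol article*

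**What the plan says.** The two assumptions stand together near the end of Aim 1 in Statistical Analyses: "Additionally, we assume that transition times are exactly observed", and "it is assumed that the distribution of health care visit times is independent of transition probabilities for simplicity (noninformative visiting process"). Both apply to the whole model.

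Remission is one of the 17 transient states. Under Substance Use Data: "The SUD remission state is captured using self-reported substance use frequency and SUD symptoms, and clinician-reported SUD remission diagnoses". Table 2 gives the criteria as "Low risk score on alcohol and substance use screen; clinically meaningful reduction on screening scores or <2 symptoms on" the DSM-5 checklist, with a remission diagnosis as a further route. Health Care Encounter Data explains the dating: "Visit timestamps are used in models to determine follow-up time and transition times".

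On the screens, Substance Use Data says that "clinicians are prompted by the EHR to conduct annual screening with patients in primary care", and that "Validated substance use screening measures assess past-year alcohol, cannabis, and other drug use". The symptom checklist goes only to patients whose screen is high risk. Study Design and Setting describes annual screening for adult group practice patients. Quantitative Study Population also admits "KPWA health insurance plan enrollees who primarily receive care outside the internal delivery system (IDS").

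**The concern.** A care state begins with a visit or a fill, so its timestamp is its start. Remission does not begin with a visit. A low-risk screen shows only that the patient improved at some time since the last assessment that did not show remission, which makes the date interval-censored. Dating it at the screen has three consequences:

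- Time in the preceding state is too long and time in remission too short. The clock resets at state entry, so the timing of exits from remission is shifted too.
- Remission that begins and ends between two assessments is not seen.
- Patients assessed more often can appear to remit more, and sooner, with the same true course. The protocol itself remarks that patients with more visits may have poorer health, which sits badly with visit timing being independent of the transitions.

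Enrollment type matters here because annual screening is described for one part of the cohort. For enrollees treated mainly outside the delivery system, clinician remission diagnoses in claims may be the main route. A remission comparison that mixes the two groups partly compares ways of detecting remission.

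**Working it through.** The protocol gives no remission count, rate or share by route, so there is no figure of its own to reproduce. What follows applies its stated intervals to the screen route alone.

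**Inputs from the protocol**
- Screening interval: annual, taken as 365 days (Substance Use Data).
- Recall window: past year (Substance Use Data).
- Ceased care: more than 194 days without a qualifying fill or service (Table 2).

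**Assumption:** the true remission date is uniform between two annual screens.

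**Step 1, delay to detection.** If the next screen shows the change at once, delay D is uniform on 0 to 365 days. Mean = 365/2 = 182.5 days; range 0 to 365.

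If instead the whole past-year window must be clear before the screen reads low risk, a further 365 days is added: mean 365 + 182.5 = 547.5 days, range 365 to 730. This is the unfavorable end. Table 2 also accepts a clinically meaningful reduction in score, which could appear sooner.

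**Step 2, competition with ceasing care.** Take a patient whose SUD care ends at remission. The chance that a screen comes within the limit is P(D ≤ 194) = 194/365 = 0.53. For the other 171/365 = 0.47 the ceasing-care rule is met first. If the full recall window must clear, the chance is 0. Patients who stay in SUD care after remission are not affected in this way.

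**Step 3, unequal detection (illustration only).** Two groups of 1,000,000 simulated patients had the same true remission hazard. One group was screened annually and the other never. All of the following are assumptions, none from the protocol: exponential remission with median 180 or 365 days; the same share of remissions coded by a clinician within 0 to 90 days in both groups; every remission visible at the next screen; 365 days of observation. The recorded rate is recorded remissions divided by time to recorded remission or day 365.

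| Share clinician-coded | Screened : unscreened rate, median 180 d | Same, median 365 d |
|---|---|---|
| 10% | 8.2 | 7.1 |
| 30% | 2.9 | 2.6 |
| 50% | 1.9 | 1.7 |

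The true ratio is 1 throughout. Recorded rates were 0.43 to 0.63 of the true rate with screening and 0.05 to 0.37 without. The ratio shrinks as clinician coding rises, and its direction depends on coding being equal in the two groups. The table shows the mechanism; it does not estimate this study's bias.

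**The case against.** The strongest reply is that remission has a third route. Clinician diagnoses are recorded at visits in both the EHR and claims, and data on externally provided services are nearly 99% complete within 6 months. Enrollees outside the delivery system are therefore not without a remission measure. Remission is also neither a terminal state nor a quality measure, no key question in Table 3 names it, and the study is exploratory. Stratification by number of outpatient visits is mentioned, the limitations acknowledge misclassification, and the covariate list is open-ended.

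Much of this stands, and it rules out several stronger readings:

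- A reader might infer that remission is seen mainly at screens, or that screening happens only in group-practice clinics. The protocol states neither. It gives no shares by route, and Table 1 allows screen-based triggers in urgent care, behavioral health and other settings.
- A reader might expect subcohorts dominated by network enrollees to show little remission. Subcohorts are defined by where the index event occurred, and no enrollment mix is given.
- A reader might set the delay against the 30 to 90 day horizons or the 1-year point. Those belong to ceasing care (Table 5) and to comparisons of terminal states, not to remission.
- A reader might say that the visiting assumption fails for care states. Their entry is the visit, so the time is observed and the assumption does little work there. It matters for remission.

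The core is not answered. A clinician diagnosis is also dated at a visit. Stratifying by visit count is conditional on feasibility and addresses neither interval censoring nor unequal screening. The limitations do not mention detection timing. Remission also competes with ceased care, so the error can reach a terminal outcome.

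**Conclusion.** The concern holds for transitions into and out of remission and for quantities derived from them. It does not extend to the timing of moves between care states. As written, the exact-time assumption conflicts with the protocol's own account of how remission is measured, and the noninformative-visit assumption is doubtful for that state.

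On the screen route, the mean delay of about 182 days and the 53% chance of meeting a screen within 194 days rest on uniform timing between annual screens and on a screen that reflects the change at once. The 53% further assumes that SUD care ends at remission. The net effect across all three routes cannot be sized from the document. The point merits a change before the models are fitted, because the core repair is cheap and the error would be hard to see in the results.

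**What to change.** In the Aim 1 assumptions:

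1. Limit the exact-time assumption to care states and death.
2. State that remission based on a screen or checklist is dated at detection and is interval-censored since the last assessment that did not show remission.
3. Include group-practice versus network enrollment, which the cohort definition already distinguishes, as a covariate or stratum for transitions into and out of remission.
4. Add sensitivity analyses that (a) use clinician-diagnosed remission only, (b) restrict remission results to group-practice enrollees, and (c) vary the remission date within its interval without moving it before an observed care visit. Unrestricted re-dating, such as a plain midpoint, could reorder the observed path and alter the clock-reset durations.

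The cost is a few more model runs, less precise remission estimates, and one more covariate against the protocol's events-per-covariate guideline (40 to 50 transitions, or 10 under the permissive threshold). No new data are needed.
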